### Data collection

2.11

Baseline assessment will be performed during the screening period. Basic information including sex, age, date of birth, date of obtaining informed consent, history of EST, presence of biliary stenting, and assessment of performance status will be recorded retrospectively. To ensure feasibility and safety, complete blood counts, hepatic and renal function tests, and biochemical tests will be performed during the screening period.

Computed tomography (CT) will be performed during the screening period to diagnose the tumor stage according to the TNM classification, to determine the site of biliary obstruction, and to determine the presence of gastric outlet obstruction. Patients will undergo the above-mentioned blood tests on post-procedure days 1, 3, 14, 30, 90, and 180 to evaluate the efficiency of the treatment, AEs, and stent dysfunction. CT will be performed postoperatively on days 1, 14, and 180 to evaluate the position of the stent, AEs, and stent dysfunction. The schedule for enrollment, interventions, and assessments is shown in Figure 3.

**Figure 3 F3:**
[figure not shown]
Standard protocol items (SPIRIT): schedule for data collection.

### Follow-up

2.12

All patients will be followed until either death or 180 days after the treatment of the last registered patient. If the patient is unable to attend hospital, follow-up will be conducted over the phone. If follow-up information cannot be obtained, the patient will be considered lost to follow-up, and their data will be documented accordingly.

## Statistical analysis

3

### Sample size calculation

3.1

In this study, we assume that the stent patency rate at 180 days after stent insertion will be 85.1% in the EUS-CDS group and 48.9% in the ERCP group.^[9]^ In this case, assuming an exponential distribution for the survival time distribution, when the null hypothesis “stent patency rates at 180 days after stent insertion in the EUS-BD and ERCP groups are the same” is tested against the 2-sided alternative hypothesis “stent patency rates at 180 days after stent insertion in the EUS-BD and ERCP groups are different,” using a two-sample log-rank test at a significance level of α = 0.01 (2-sided), the number of events required to achieve a power of 1-βof 90% is 29. If the enrollment period is 12 months, the observation period after the last case enrollment is 6 months, and the death rate per month is 10.0% in both groups, then the minimum number of cases required is 90. Therefore, we have set a target number of 95 cases, assuming 5% are ineligible.

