### Primary endpoint

2.9

The primary endpoint is the stent patency rate at 180 days after stent insertion. The stent patency rate is defined as the percentage of patients who do not experience stent dysfunction from the date of stent insertion to 180 days after treatment.

Stent dysfunction is defined as follows:

1.If the lowest serum total bilirubin (T-Bil) value in the blood tests performed after treatment is <1.5 mg/dL: a serum T-Bil level of ≥3.0 mg/dL and a bile duct diameter greater than that on the pretreatment imaging.2.If the lowest serum T-Bil value in the blood tests performed after treatment is more than 1.5 mg/dL: a serum T-Bil level >2.0 times the lowest value and a bile duct diameter greater than that on the pretreatment imaging.

Patients who are lost to follow-up or who die without stent dysfunction will be censored at the last observation date. Patients without technical success will be censored at the treatment date.

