### Statistical analysis

3.2

In the effectiveness analysis for the population, analysis of the full analysis set is the main analysis, and per protocol analysis is performed as a reference. The safety analysis for the target population will analyze all test examples. For the stent patency rate at 180 days after stent insertion, the *P* value for the difference between the two procedures will be calculated using a 2-sample log-rank test. The Kaplan–Meier method will be used to estimate survival curves for each group. Greenwood's formula will be used to estimate the confidence interval for the stent patency rate at 180 days after stent insertion, and Brookmeyer and Crowley's method will be used to estimate the confidence interval for the median rate. For the rates of technical success, clinical success, technical success in cases not requiring fistulous-tract dilation, procedure-related AEs, re-intervention success, and patients receiving post-drainage chemotherapy, the percentages, and 99% confidence intervals will be calculated for each group. For the procedure time, the mean and 99% confidence interval will be calculated for each group. For the overall survival time, the *P* value for the difference between the 2 groups will be calculated with a 2-sample log-rank test. A *P* value of ≤.01 will be considered statistically significant. All analyses will be performed using JMP Pro version 14 (SAS Institute, Inc., Cary, NC).

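### The 29 events from 90 patients count stent dysfunctions up to 18 months, but the primary endpoint stops at day 180 and the log-rank window is not stated

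*Protocol article*

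**What the plan says.** The endpoint (section 2.9) is the proportion of patients without stent dysfunction "from the date of stent insertion to 180 days after treatment". Patients who are lost or who die without dysfunction are censored at their last observation.

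The sample size (section 3.1) assumes that "the stent patency rate at 180 days after stent insertion will be 85.1% in the EUS-CDS group and 48.9% in the ERCP group", "assuming an exponential distribution for the survival time distribution". It states both hypotheses as 180-day patency rates and uses a log-rank test at two-sided alpha 0.01. For 90% power it requires 29 events. The step from events to patients begins "If the enrollment period is 12 months, the observation period after the last case enrollment is 6 months", adds a 10% monthly death rate in both arms, and arrives at 90 patients, raised to 95 for 5% ineligible.

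The analysis (section 3.2) introduces the primary log-rank P value with "For the stent patency rate at 180 days after stent insertion". It gives no time at which the test is cut.

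On observation, section 2.11 says "Patients will undergo the above-mentioned blood tests on post-procedure days 1, 3, 14, 30, 90, and 180", and the last listed CT is also on day 180. Section 2.12 says that patients are "followed until either death or 180 days after the treatment of the last registered patient", so early patients are followed well past day 180.

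**The concern.** Two time windows are in play. The endpoint, both hypotheses and the listed assessments stop at day 180. The sample size counts events for as long as each patient is under observation, up to 18 months for the first patient enrolled. A log-rank test draws its power from the number of events, so the window decides the power.

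Which window the test uses also decides which events enter the primary P value. If the protocol leaves that open, it could be settled after the data are seen. If the test is cut at day 180, the stated 90% power belongs to an analysis that will not be done.

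**Working it through.** **Inputs** (section 3.1, with 1:1 allocation from section 2.6): 180-day patency 85.1% and 48.9%; exponential times; two-sided alpha 0.01; power 90%; 12 months of enrolment plus 6 months of observation; 10% deaths per month. Assumptions made here: uniform enrolment, 180 days taken as 6 months, and the death rate read either as a hazard of 0.10 or as -ln(0.9) = 0.1054. The steps below use 0.1054; ranges cover both readings.

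**Hazards per month.**
- EUS-CDS: -ln(0.851)/6 = 0.0269
- ERCP: -ln(0.489)/6 = 0.1192
- Hazard ratio: ln(0.851)/ln(0.489) = 0.2255

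**Required events.** Schoenfeld: 4 × (2.576 + 1.282)² / (ln 0.2255)² = 26.8, so 27. Freedman gives 38. Lakatos gives 29.6 without deaths and 31 with them. The stated 29 lies among the standard variants and is taken as given.

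**The protocol's figure, with 6 to 18 months of follow-up.** Let l be the dysfunction hazard, m the death hazard and k = l + m. The chance of an observed dysfunction is

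(l/k) × {1 − [exp(−6k) − exp(−18k)]/(12k)}.

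- EUS-CDS: k = 0.1323, giving 0.2033 × (1 − 0.2267) = 0.157
- ERCP: k = 0.2246, giving 0.5309 × (1 − 0.0899) = 0.483
- Events in 90 patients: 45 × (0.157 + 0.483) = 28.8 (29.4 with death hazard 0.10)
- Patients needed for 29 events: 88.8 to 90.6

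The stated 90 is reproduced.

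**The same 90 patients, each cut at day 180.** The chance becomes (l/k) × [1 − exp(−6k)].

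- EUS-CDS: 0.2033 × (1 − 0.4523) = 0.111
- ERCP: 0.5309 × (1 − 0.2599) = 0.393
- Events: 45 × (0.111 + 0.393) = 22.7 (23.0 with death hazard 0.10)
- Patients needed for 29 events by day 180: 113.5 to 115.0

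About 28.8 − 22.7 = 6.1 planned events, or 21%, therefore fall after day 180.

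**Power.** Schoenfeld: Φ(√d × |ln HR|/2 − 2.576), with |ln HR|/2 = 0.745. For d = 28.8 this is Φ(1.42) = 92%; for d = 22.7 it is Φ(0.97) = 83%. The log-rank test was also simulated with 20,000 runs per setting.

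| Patients, window | Events | Schoenfeld | Simulated |
|---|---|---|---|
| 90, 6-18 months | 28.8-29.4 | 92-93% | 87.5-88.6% |
| 90, day 180 | 22.7-23.0 | 83-84% | 75.4-76.5% |
| 95, day 180 | 24.0-24.4 | 86% | 78.7-79.3% |

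Lakatos agrees with the simulation: 87-88% over the longer window and 74% at day 180, with 90 patients. In the simulations, 90 patients reached 29 events by day 180 in 7-8% of runs.

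Compared within one method, the loss is about 9 points (Schoenfeld) or 12 points (simulation). The chance of missing the planned effect roughly doubles: from 7-8% to 16-17%, or from about 12% to about 24%.

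**The case against.** The strongest reply is that the protocol never cuts the log-rank test at day 180. Section 2.9 censors at the last observation, section 2.12 follows everyone until 180 days after the last patient's treatment, and that matches the 12 + 6 month design in 3.1. On this reading the test uses all follow-up, 180-day patency is read off the Kaplan-Meier curve, and 29 events, 90 patients and 90% power stand together. This is a coherent reading and it cannot be excluded. It does not remove the inconsistency, because the endpoint as worded in 2.9 excludes the later dysfunctions.

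The planned interval for the median in 3.2 does not settle the window. Under the planning assumptions the ERCP median is 0.693/0.1192 = 5.8 months, just inside day 180. The EUS-CDS median is 0.693/0.0269 = 25.8 months, beyond either window.

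A reader might infer that a log-rank test over all follow-up would test the wrong hypothesis. Under the exponential model stated in 3.1, equal 180-day rates and equal hazards are the same null. The two part company only if that model fails.

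A reader might also infer that dysfunction is not ascertained after day 180. The documents show only that no blood test or CT is listed after that day. Follow-up continues, by telephone only for patients who cannot attend, and the schedule figure is not shown. Still, the definition of dysfunction needs a bilirubin value and duct imaging, which a telephone call does not supply.

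**Conclusion.** The point holds as an inconsistency between the endpoint and the sample size, with a power loss that depends on the window. It is not an arithmetic error: the 90 patients follow from the stated inputs. Nor do the documents show that the trial is underpowered, since the test window is not stated. What they do show is that 29 events from 90 patients belongs to follow-up of 6 to 18 months, not to the 180-day endpoint. If the test follows that endpoint, expect about 23 events and power of about 75% (simulated) to 84% (Schoenfeld); all 95 patients raise this to about 24 events and 79% (simulated) or 86% (Schoenfeld).

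The result rests on the protocol's own patency and death rates, exponential times and uniform enrolment. Neither reading of the 10% death rate closes the gap, and even Schoenfeld's lower requirement of 27 events exceeds 23.

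Technical failures, censored at the treatment date under 2.9, would lower the count further. No figure is put on this: the protocol reports 95% technical success for EUS-CDS with this stent but gives no rate for ERCP.

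**What to change.** State in 2.9 and 3.2 whether dysfunctions after day 180 enter the primary log-rank test, and make 3.1 match. Either choice is workable.

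1. **Keep the day-180 window.** Say that patients free of dysfunction are censored at day 180, and restate 3.1 as about 23 expected events and about 75-84% power, naming the method behind each figure. No extra patients are proposed. The cost is a less favourable stated power.
2. **Use all follow-up.** Say so explicitly, keep 29 events, and report 180-day patency as the Kaplan-Meier readout. Record bilirubin, imaging and re-intervention data from routine care after day 180. The cost is a changed wording of a registered primary endpoint and some added data capture from patients who are already being followed.

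The choice should be made and dated before any comparative results are seen.

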### Statistical analysis

3.2

In the effectiveness analysis for the population, analysis of the full analysis set is the main analysis, and per protocol analysis is performed as a reference. The safety analysis for the target population will analyze all test examples. For the stent patency rate at 180 days after stent insertion, the *P* value for the difference between the two procedures will be calculated using a 2-sample log-rank test. The Kaplan–Meier method will be used to estimate survival curves for each group. Greenwood's formula will be used to estimate the confidence interval for the stent patency rate at 180 days after stent insertion, and Brookmeyer and Crowley's method will be used to estimate the confidence interval for the median rate. For the rates of technical success, clinical success, technical success in cases not requiring fistulous-tract dilation, procedure-related AEs, re-intervention success, and patients receiving post-drainage chemotherapy, the percentages, and 99% confidence intervals will be calculated for each group. For the procedure time, the mean and 99% confidence interval will be calculated for each group. For the overall survival time, the *P* value for the difference between the 2 groups will be calculated with a 2-sample log-rank test. A *P* value of ≤.01 will be considered statistically significant. All analyses will be performed using JMP Pro version 14 (SAS Institute, Inc., Cary, NC).

## Adverse event reporting

4

### Definition of an AE

4.1

An AE is defined as any unfavorable or unintended illness or disability and its manifestations occurring in a subject up to 14 days after the end of the protocol treatment, regardless of whether it is causally related to the protocol treatment. A clinically significant worsening of symptoms that existed before the study is also considered an AE. However, worsening of the primary disease is not included as an AE. Physiological changes that are not considered clinically important in terms of frequency or severity will not be considered as AEs. If an AE is observed in a subject, then the principal investigator (or sub-investigator) will immediately ensure the safety of the subject, take appropriate measures, and describe the event in the case report.

In principle, CTCAE v5.0 should be used for the evaluation of adverse events/adverse reactions. However, for the following events, diagnosis, and severity assessment should be performed according to the respective criteria.

1.Postprocedural pancreatitis: Cotton criteria.^[12]^2.Cholecystitis, nonocclusion cholangitis, stent migration, stent deviation, liver abscess, bleeding, intestinal perforation, and abdominal pain: ASGE guidelines.^[13]^

### Definition of a serious adverse event

4.2

A serious adverse event is an AE occurring during the procedure or any time after the procedure that fulfills ≥ of the following criteria:

1.Results in death2.Is immediately life-threatening3.Requires in-patient hospitalization or prolongation of existing hospitalization4.Results in persistent or significant disability or incapacity5.A congenital abnormality or birth defect

The principal investigator of the institution where the serious AE occurs should take appropriate measures, regardless of whether or not there is a causal relationship with the research, and should immediately report the details of the event to the head of the research institution and the principal investigator, in accordance with the regulations of the respective medical institution.

### Monitoring

4.3

Visit monitoring will be performed once a year by an independent data monitoring committee. The monitoring committee will collect information on the status of accumulation, inclusion/exclusion criteria, serious AEs, and any other relevant information, and strive to provide feedback to participating institutions for early resolution if there are any problems. The monitoring committee will also report any serious AEs to the committee for efficacy and safety assessment.

## Discussion

5

This multicenter single-blinded RCT study is designed to assess whether EUS-CDS with a novel stent shows superior stent patency to ERCP with a traditional metal stent when used for the first-line drainage of malignant distal biliary obstruction. This clinical trial will also compare the rates of technical success, clinical success, procedure-related AEs, re-intervention success, patients receiving post-drainage chemotherapy, and procedure and overall survival time.

Currently, the criterion standard procedure for malignant biliary drainage is transpapillary drainage with ERCP, whereas EUS-CDS is the modality of choice when ERCP fails in patients with distal bile duct obstruction. The major problem affecting transpapillary drainage with ERCP is stent dysfunction due to tumor tissue stent ingrowth and/or overgrowth.^[3,4]^ By contrast, stent tumor tissue ingrowth or overgrowth does not occur after EUS-CDS because the drainage route passes beside the tumor. Therefore, EUS-CDS is expected to have longer stent patency than ERCP. If stent patency rate is shown to be higher in EUS-CDS than in ERCP, it would be clinically significant because it would not only reduce the number of re-interventions, but could also affect oncologic outcomes. In patients with unresectable pancreatic cancer with a good performance status, there is a clear survival benefit attributable to FOLFIRINOX therapy^[14]^ and nab-paclitaxel plus gemcitabine therapy,^[15]^ which are delayed if re-interventions for biliary obstruction are needed.

Post-ERCP pancreatitis (PEP) is a major complication of ERCP.^[16–19]^ PEP is caused by injury to the pancreatic duct during insertion of a catheter, guidewire, or stent into the duodenal papilla. Treatment of PEP often takes a long time and delays the start or resumption of chemotherapy. By contrast, as EUS-CDS does not involve the duodenal papilla, it has little effect on the pancreatic duct and rarely leads to pancreatitis. However, a serious problem with EUS-CDS is the occurrence of AEs such as bile leakage and stent migration in 17.9% to 23.3% of cases.^[20,21]^ The main reasons for the high rate of AEs are the technical complexity of the procedure and the lack of dedicated equipment. Therefore, we developed a metal stent suitable for EUS-CDS (Covered BileRush Advance, Piolax Medical Devices, Yokohama, Japan).^[8]^ We also reported a prospective multicenter study that found that EUS-CDS with this metal stent was associated with 95% technical and 100% clinical success rates, with procedure-related AEs reported in only 5% of cases.^[8]^ In 31.6% (6/19) of procedures, the delivery system was successfully inserted into the bile duct without requiring a fistulous-tract dilatation device. This stent has two advantages over conventional stents. First, the delivery system, which comprises a thin shaft (7.5Fr.) and a tapered tip (2.6Fr.), facilitates successful insertion into the bile duct without the use of fistulous-tract dilation, thereby preventing bile leakage during the procedure. Second, the stent is made from laser-cut wire and has a flare structure at both ends, features that may help to prevent stent migration. EUS-CDS using this novel thin delivery system stent might cause fewer AEs than EUS-CDS with a standard stent, especially bile peritonitis and stent migration. Recently, the delivery system for this metal stent was further reduced in diameter (7.0Fr) to reduce the need for fistulous-tract dilation.^[7]^ This trial will use this thinner delivery system stent (7.0Fr), and it is therefore expected that it will be possible to insert the delivery system into the bile duct without the use of fistulous-tract dilation in a higher proportion of cases.

Recently, three RCT studies compared EUS-BD and ERCP in first-line biliary drainage.^[9–11]^ One study reported that EUS-BD had a higher rate of stent patency and a lower rate of procedure-related AEs than ERCP, while two studies reported that EUS-BD had comparable stent patency and AE rates to ERCP. Two of these three RCT studies were subject to the major limitations that they were single-center studies and included only a small number of patients.^[10,11]^ Although the other study included a larger number of patients, it was subject to the major limitation that it included techniques other than EUS-CDS (such as EUS-guided hepaticogastrostomy) in the EUS-BD group, and did not make an actual comparison between ERCP and EUS-CDS. We believe that our study will be superior to these three studies in that it is a multicenter study, it will include statistically sufficient sample sizes, and it will perform actual comparisons between ERCP and EUS-CDS, with the EUS-CDS being performed using the more suitable novel stent.

## Conclusions

6

This study is designed to assess whether EUS-CDS with a novel stent is superior in terms of stent patency to ERCP when the procedures are used for first-line drainage of malignant distal biliary obstruction. If EUS-CDS is superior to ERCP for first-line drainage for malignant distal biliary obstruction in terms of stent patency and safety, it is expected that interruption to chemotherapy due to stent dysfunction and adverse effects will be avoided, and that EUS-CDS may replace ERCP as the first-line drainage method.
